### Outcome measures

#### Primary objective

The primary outcome measure for the primary objective will be the symptom onset or last known well time to groin puncture time (start of EVT) in patients with an ischaemic stroke with LVO who presented in the emergency department within 6 h from stroke onset. Secondary outcome measures for the primary objective will be the symptom onset to needle time (start of IVT) in patients who are treated with IVT, the percentage of patients with ischaemic stroke treated with IVT within the conventional guideline-recommended time window of 4.5 h after symptom onset or last seen well, the percentage of patients with ischaemic stroke treated with EVT within the conventional guideline-recommended time window of 6 h after symptom-onset or last seen well and the mRS score after 3 months.

#### Secondary objective

For the secondary objective, outcome measures will be the distribution of final diagnoses (ischaemic stroke with LVO, ischaemic stroke without LVO, TIA, intracerebral haemorrhage and stroke mimics) in PSC and intervention centres, the number and percentage of ischaemic stroke patients without EVT-eligible occlusion taken to an intervention centre after bypassing a PSC (overtriage), the number and percentage of ischaemic stroke patients with an EVT-eligible occlusion who were not bypassed to an intervention centre (undertriage), the number of triages per month, number of users per month, number of uses per paramedic per month, compliance, adherence to the Stroke Triage App advice, total number of required acute ambulance transportations (prior to reperfusion therapy) and total number of required subacute ambulance transportations (transfers after reperfusion therapy or in absence of an indication thereof).

### Sample size calculation

Under the initial assumption that the Stroke Triage App would be used for all eligible cases and within the context of an implementation study running for 12 months, a power calculation rather than a sample size calculation was conducted. A mean (±SD) onset-to-groin time of 224.5 (±94.1) min was extracted from the Dutch MR CLEAN registry. Based on modelled data, where the Stroke Triage App algorithm has been applied to a prospectively collected cohort of prehospital suspected stroke patients, the mean effect of implementation of triage with the Stroke Triage App algorithm on the primary outcome measure (onset-to-groin time in patients undergoing EVT for ischaemic stroke with LVO) in the intervention region is estimated to be −31 min.^21^ We assumed a low intra-cluster correlation coefficient (ICC) of 0.01, as the primary outcome, onset-to-groin time, is substantially influenced by onset-to-alarm time. This interval is highly variable and largely determined by patient-specific and situational factors, such as stroke severity, aphasia, the presence of witnesses and time of symptom onset, which are largely independent of cluster membership. We also expected limited between-cluster variability. Public stroke-awareness campaigns are implemented nationally, acute stroke care is standardised through national guidelines and the study regions are comparable in terms of urbanisation. Together, the high within-cluster variability and limited between-cluster variability support the assumption of a low ICC in this study.

Based on previous stroke registry analyses, 96 EVTs annually in the intervention region would be required to reach a power of 80%. It was estimated that approximately 400 EVTs take place annually in the intervention region, which corresponds to a power of > 99% at a predefined alpha of 0.05.^22^ A sample size analysis for the secondary objective was not applicable.

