### Data analysis plan

The statistical analysis will be performed after inclusion of the last patient, after the data have been checked, errors have been corrected and the database has been locked. Missing data will be handled via simple imputation (if < 5% missing) or multiple imputation by means of a multiple regression model (if ≥ 5% missing). We will estimate the effect of the implementation of the Stroke Triage App on the primary and secondary outcomes of the primary objective using difference-in-differences linear regression analysis. This analysis compares the differences before and after implementation in the implementation region with the differences between the same periods in the control region where no implementation takes place. This method adjusts for unobserved confounders and (other) time-related differences in acute stroke care. For the secondary objective, we will report the observed outcomes in the study cohort. We will then conduct counterfactual simulation assuming transport to the nearest hospital, in accordance with the ambulance protocol that was in place prior to the implementation of the Stroke Triage App (“drip-and-ship” model). We will compare the observed outcomes with the simulated outcomes in order to be able to make a statement about the effects of the implementation of the Stroke Triage App on these outcomes. Closure of the database and analysis of the data is planned after submission of the protocol for publication. A detailed Statistical Analysis Plan can be found in the Supplementary Materials.

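### 96 EVTs a year does not give 80% power for the planned difference-in-differences analysis, and the >99% at 400 a year is slightly high on the stated 12-month basis

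*Protocol article*

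**What the plan says.** The Sample size calculation section of the protocol article assumes a 12-month study in which the app is used for every eligible case. It gives these inputs:

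- Outcome distribution: "A mean (±SD) onset-to-groin time of 224.5 (±94.1) min was extracted from the Dutch MR CLEAN registry".
- Effect: the mean change in onset-to-groin time "in the intervention region is estimated to be −31 min".
- Clustering: "We assumed a low intra-cluster correlation coefficient (ICC) of 0.01".

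It then states that "96 EVTs annually in the intervention region would be required to reach a power of 80" per cent, that "approximately 400 EVTs take place annually in the intervention region", and that this volume means "a power of > 99% at a predefined alpha of 0.05". It gives no sidedness, no before-period or control-region EVT counts, and no definition of the cluster.

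The Data analysis plan section fixes DID linear regression for the primary outcome, an analysis that "compares the differences before and after implementation in the implementation region with the differences between the same periods in the control region". The Study population section sets 24 months before and 24 months after implementation in both regions, with about 1.8 million inhabitants in the intervention region and 2.8 million in the control region.

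**The concern.** A DID estimate is a difference between two differences, so its variance is the sum of four cell-mean variances. With equal cells, that is twice the variance of a simple two-group comparison. A requirement of 96 a year looks too small even for two groups with these inputs, and more so for four cells.

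The pair of figures, 96 needed and 400 expected, presents the study as having roughly four times the EVTs it needs (400/96 = 4.2). If the 96 is wrong for the planned contrast, a reader is misled about how much margin there is for a smaller effect, for low app use or for clustering.

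**Working it through.** **Inputs.** From the Sample size calculation section: SD 94.1 min, effect 31 min, alpha 0.05, 96 and 400 EVTs a year. From the Study population section: populations 1.8 and 2.8 million, 24+24 months. Assumptions: two-sided test (one-sided also shown), independent patients, and a control region either equal in EVT volume or larger by k = 2.8/1.8 = 1.556.

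**Step 1: the plan's own figures.** Base term: (1.960 + 0.842)² × 94.1² / 31² = 7.849 × 8854.8 / 961 = 72.3.

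- Two-group comparison: 2 × 72.3 = 144.6, so 145 per group (114 one-sided). With 96 per group, power is 62.6% (73.8% one-sided). The 96 is not reproduced.
- 400 against 400 gives 99.65%. The >99% is reproduced, but by a two-group comparison and not by a DID.

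**Step 2: DID power.** SE = 94.1 × √(1/n₁₁ + 1/n₁₀ + 1/n₀₁ + 1/n₀₀), and power = Φ(31/SE − 1.96). The yearly number applies to both intervention-region periods.

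Example, 96 a year, 12+12 months, equal regions: SE = 94.1 × √(4/96) = 19.21; 31/19.21 = 1.614; Φ(−0.346) = 36.5%.

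Example, 96 a year, 24+12 months, scaled control (cells 192, 96, 299, 149): SE = 15.08; 31/15.08 = 2.056; Φ(0.096) = 53.8%.

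The number needed each year for 80% is 72.3 times the multiplier shown, rounded up.

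| Months before + after | Control | Power at 96/yr, two-sided (one-sided) | Power at 400/yr, two-sided (one-sided) | EVTs/yr for 80%, two-sided |
|---|---|---|---|---|
| 12+12 | equal | 36.5% (48.8%) | 90.9% (95.0%) | ×4 = 290 |
| 12+12 | scaled | 42.9% (55.4%) | 95.3% (97.7%) | ×(2 + 2/k) = 238 |
| 24+12 | equal | 46.2% (58.7%) | 96.7% (98.5%) | ×3 = 217 |
| 24+12 | scaled | 53.8% (66.0%) | 98.7% (99.5%) | ×(1.5 + 1.5/k) = 179 |
| 24+24 | equal | 62.6% (73.8%) | 99.7% (99.9%) | ×2 = 145 |
| 24+24 | scaled | 71.2% (80.9%) | 99.9% (>99.9%) | ×(1 + 1/k) = 119 |

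**Step 3: how far the control size could rescue the 96.** With an unlimited control region, only the two intervention cells contribute. At 96 a year, two-sided power is then 62.6% (12+12), 75.0% (24+12: SE = 94.1 × √(1.5/96) = 11.76) and 89.8% (24+24). With a 12-month after-period and 12 or 24 months before, no control size brings 96 a year to 80% two-sided.

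**Step 4: clustering.** A centre effect that is constant over time largely cancels in a DID. A centre effect that changes between periods does not cancel, and it adds variance that more patients per centre cannot remove. The article gives the ICC but neither the cluster nor how much of the ICC varies by period, so only the direction can be stated: every power in the table would fall.

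**The case against.** The strongest defence has four parts.

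- **The 96 may be only the exposed cell.** If it counts only EVTs after implementation, with the other cells at full volume (800 before; 1,244 and 622 control, scaled), DID power is 79.3%, close to the stated 80%. But this needs 24+12 months, scaled controls and no clustering; with 12 months before (400; 622 and 622) it is 73.7%. It also sits badly with the article's wording, which describes a yearly EVT volume in the region and so would apply before implementation too.
- **The layout now planned is more favourable.** This stands in part. With 24+24 months, 96 a year gives 63–71% two-sided and reaches 80% only with a one-sided test and scaled controls (about 94 a year needed) or with a far larger control region. The article states neither.
- **The conclusion at 400 a year hardly moves.** This stands. Without clustering, power at the full effect exceeds 90% in every layout, and exceeds 99% with 24+24 months.
- **The figures were initial, and an article condenses.** The Duration and current status section reports a later re-estimation, and a formula may be left to the full plan. That excuses the absence of a formula. It does not excuse a printed figure that fails on the inputs printed beside it.

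**Conclusion.** The statement that 96 EVTs a year gives 80% power does not hold for the planned DID analysis. Two-sided power is about 36–54% with a 12-month after-period and about 63–71% with 24+24 months. The yearly requirement for 80% is about 179–290 and 119–145 respectively. The >99% at 400 a year is slightly overstated on the 12-month basis (about 91–99% under these control sizes) and correct with 24+24 months, in each case before cluster-by-period variation. The results rest on a two-sided test, independent patients and a control region equal in volume or scaled by population.

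Stronger conclusions that a reader might infer are not supported:

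- **That 36–54% is a ceiling.** It is not: 24+24 months gives more, and an unlimited control region gives more still.
- **That the source of the 96 is known.** A comparison with 1:3 allocation gives 72.3 × 4/3 = 96.4. A one-sample number with design effect 1 + (400/12 − 1) × 0.01 = 1.323 gives 95.7. The article documents neither.
- **That a particular loss from clustering can be quoted.** This would need a cluster definition and a between-period correlation that the article does not give.
- **That the later figure of 274 inherits this error.** The Duration and current status section does not state the method behind it.
- **That the study is underpowered at 400 a year and −31 min.** The unclustered figures say otherwise.

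**What to change.** Replace the 96, and the >99% as stated for a 12-month study, with a calculation for the DID contrast:

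- Variance = SD² × (1/n₁₁ + 1/n₁₀ + 1/n₀₁ + 1/n₀₀), plus a cluster-by-period term derived from the stated ICC.
- State the four cell sizes, including the expected control-region EVT volume, the sidedness of the test, what a cluster is and how many there are per region. State also the share of the ICC variance assumed to change between periods, and vary it.
- Report the required number and the power at 400 a year for both the original 12-month design and the extended 24+24-month design.

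This changes text only and alters neither the data collection nor the analysis. The sponsor has to supply the planning count for the control region and the cluster definition. The cost is that the stated requirement rises and the 12-month power becomes somewhat less favourable.

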### Data analysis plan

The statistical analysis will be performed after inclusion of the last patient, after the data have been checked, errors have been corrected and the database has been locked. Missing data will be handled via simple imputation (if < 5% missing) or multiple imputation by means of a multiple regression model (if ≥ 5% missing). We will estimate the effect of the implementation of the Stroke Triage App on the primary and secondary outcomes of the primary objective using difference-in-differences linear regression analysis. This analysis compares the differences before and after implementation in the implementation region with the differences between the same periods in the control region where no implementation takes place. This method adjusts for unobserved confounders and (other) time-related differences in acute stroke care. For the secondary objective, we will report the observed outcomes in the study cohort. We will then conduct counterfactual simulation assuming transport to the nearest hospital, in accordance with the ambulance protocol that was in place prior to the implementation of the Stroke Triage App (“drip-and-ship” model). We will compare the observed outcomes with the simulated outcomes in order to be able to make a statement about the effects of the implementation of the Stroke Triage App on these outcomes. Closure of the database and analysis of the data is planned after submission of the protocol for publication. A detailed Statistical Analysis Plan can be found in the Supplementary Materials.

### Patient and public partnership

Patients and the public were not involved in the design of this study. The Erasmus MC Stroke Center Patient Panel was involved in the design of patient information forms and was consulted regarding the opt-out procedure. A user council consisting of paramedics was established and consulted during various phases of the study, including development, implementation and evaluation of the application. Furthermore, the study protocol, patient information forms, progress of the study and specific information for patients, researchers and healthcare professionals are publicly available on the project website (www.stroketriageapp.com).

### Duration and current status of the study

The study started on 22nd January 2024, when the Stroke Triage App went live and was incorporated into the regional protocols for ambulance care. Due to lower-than-expected compliance and usage of the Stroke Triage App, the study protocol was amended to facilitate an interim analysis allowing for re-estimation of the sample size. During this interim analysis at 9 months after implementation, the usage rate of the Stroke Triage App was evaluated. It was determined that the Stroke Triage App was used for triage in 33% of patients eligible for EVT. Based on the revised effect size of the intervention, a new sample size calculation was conducted. Assuming a reduced effect size of 33%, we estimated that the Stroke Triage App would need to be used for triage of 274 patients eligible for EVT in the national DASA registry. Therefore, the study group decided that the study duration could be prolonged by a maximum of 12 months. Initially, enrolment was planned to finish on 22nd January 2025. This deadline was extended to 31st December 2025 to meet the requirement of the new sample size calculation.

### Ethical aspects and informed consent

The study will be conducted according to the principles of the Declaration of Helsinki (October 2013), Gedragscode Gezondheidsonderzoek 2022, the Dutch Medical Treatment Contracts Act (WGBO) and the General Data Protection Regulation (GDPR). The Stroke Triage App is an MDR risk class I CE-marked software as a medical device used within the scope of its intended purpose. This study is part of post-market clinical follow-up and does not comprise additional invasive or burdensome procedures compared to standard of care. As such, it falls outside the scope of chapter VI of the MDR (EU no 2017/745). The Institutional Review Board of the Erasmus MC has reviewed the study protocol and confirmed that the Dutch Medical Research Involving Human Subjects Act (WMO) is not applicable.

For the primary objective, non-personally identifiable data collected as part of a national quality registry (Dutch Acute Stroke Audit) will be used, in which all Dutch hospitals participate. These data are collected with an exemption from patient consent, as is common practice in clinical audits. Hospitals are free to determine who carries out the data registration (for example, [research] nurses, data managers or neurologists), but the final responsibility lies with the neurologist.

For the secondary objective, paramedics include patients with suspected stroke. Many patients with a stroke have a language impairment, anosognosia or other cognitive symptoms that complicate an informed consent procedure. A representative of the patient is often not immediately present in the prehospital setting. Moreover, a proper informed consent procedure takes time, which is not available in the ambulance. Taking informed consent afterwards (“deferred consent”) during hospitalisation is burdensome for both the patient and family and would have to be conducted by the attending physician within the context of the WGBO. Because the patients spread in various directions after the initial ambulance ride, a disproportionate number of healthcare providers or physicians from a multitude of specialties (neurologists, emergency physicians, internists, geriatricians, cardiologists and general practitioners) must be involved in order for the deferred consent procedure to take place. Because consent cannot reasonably be requested given the nature and purpose of the research, an appeal is made to the exception of Section 7:458(1)(b) of the Dutch Civil Code, as stated in Chapter 5, Section 5.4 of the 2022 Code of Conduct for Health Research. The magnitude of the effort that must be made by a large number of healthcare providers to obtain consent from the participating patients is disproportionate in relation to the relatively limited sensitivity of the collected personal data and the associated limited infringement of the personal living atmosphere. Moreover, the risks of participating in the study are minimal and using a deferred consent procedure could reasonably be presumed to lead to a drop-out of selected groups of patients due to geographical and/or clinical characteristics. This could jeopardise the validity and the reliability of the results and may lead to erroneous conclusions, making it unethical to conduct the study altogether.

Because of the aforementioned reasons, an opt-out procedure will be used. The attending paramedic will provide a patient information form in which the patient is informed about the study. This form also states that data has been collected in the ambulance and that routinely collected data from the hospital will be requested for further analysis. Patients or their next of kin are given the opportunity to object to the use of these data for the study. When a patient or next of kin objects, all data will be destroyed and this patient will no longer be included in the study.

### Dissemination plan

The study results will be disseminated to the broader public through publication in international peer-reviewed journals and by presentations at international conferences. Representatives of the participating hospitals and ambulance services will be invited as co-authors as stipulated in the data transfer agreements and asked to critically review the manuscript, in accordance with the recommendations of the International Committee of Medical Journal Editors. We plan to disseminate the results of planned secondary analyses in multiple separate manuscripts. The opt-out procedure does not provide for sharing of data with other research groups in the future, but collaborations will be possible by reaching out to the primary investigator.

## Discussion

In recent years, a variety of tools have been developed to aid paramedics in prehospital transportation decision-making for patients with acute ischaemic stroke. These tools were initially developed to rapidly identify patients with EVT-eligible stroke in order to allow direct transportation to an intervention centre, whilst ensuring that patients with non-EVT-eligible stroke are not subjected to unnecessary delays in care.^23^ Despite significant advances in prehospital diagnostic tools, optimisation of prehospital stroke care pathways remains challenging and studies investigating the implementation of prehospital stroke scales have reported heterogeneous results.^17^^,^^24^ This may in part be explained because other factors, such as stroke severity, geographical factors, driving times and transfer times and hospital-specific workflow times, were unaccounted for.^19^^,^^25^ Many of these tools fail to adequately incorporate these critical region-specific factors, limiting their applicability across existing heterogeneous stroke-care systems.^26^

Within this context, this study has several notable strengths. The Stroke Triage App contains a decision model incorporating the most important aforementioned variables to calculate the probability of a good functional outcome for 2 transportation strategies for each individual patient. This personalised approach to prehospital triage allows for the Stroke Triage App to more easily be implemented in other regions with different regional characteristics. Prior to implementation of the Stroke Triage App, the effectiveness of the triage algorithm was established through modelling in a real-world cohort of suspected stroke patients in the region, supporting implementation of the application as a CE-compliant medical device.^21^ To evaluate the effectiveness of implementation of the Stroke Triage App, we considered utilising a randomised controlled trial design, but this approach would come with significant drawbacks. First, patient inclusion and randomisation to different transportation strategies would be a time-consuming process, adversely affecting the study population with treatment delays. Second, individual patient randomisation would likely have resulted in contamination of the control arm. After training in the use of the Stroke Triage App, paramedics may consciously or subconsciously incorporate the app’s triage logic into decision-making for patients allocated to standard care. This would diminish the contrast between intervention and control conditions and compromise the ability of the study to estimate the true effect of implementation. Third, the study aimed to evaluate the effectiveness of actual implementation of prehospital triage with the Stroke Triage App, including factors such as suboptimal paramedic compliance and non-adherence to the advice due to unforeseen circumstances. Finally, obtaining informed consent prior to or deferred consent after inclusion posed substantial logistical challenges, as previously described in the Methods section. Given that the Stroke Triage App was implemented as part of routine clinical care, we chose to utilise a pragmatic, non-randomised controlled before-and-after intervention design instead. This quasi-experimental design enables comparison with a control group, while the difference-in-differences analysis also adjusts for temporal trends in the improvement of treatment times for acute ischaemic stroke. One challenge in the study design was identifying a comparable control region without prehospital triage. Although distances between PSCs and intervention centres differed slightly between regions, these differences were stable over time and are therefore unlikely to bias the estimated intervention effect. As such, we expect the between-region differences before and after implementation to primarily reflect underlying temporal trends. Another challenge of this study was selecting an appropriate outcome measure. Onset-to-groin time in patients undergoing EVT reflects the potential benefits of the intervention, whereas onset-to-needle time in patients receiving IVT reflects its potential adverse consequences. A composite outcome was considered, but this was not feasible due to the expected high proportion of missing 3-month mRS scores in the DASA registry. Moreover, combining these time-based outcomes was methodologically challenging, as minutes gained in onset-to-groin time are not directly comparable to minutes lost in onset-to-needle time. To account for patients who may have forgone treatment as a result of triage decisions, we additionally report the proportion of patients receiving EVT and IVT.

In summary, the PRESTO-2 study is distinctive in its evaluation of real-world implementation of a novel prehospital triage tool, the Stroke Triage App, in patients with suspected stroke. The tool incorporates a decision model that integrates various essential variables such as stroke severity, time since stroke onset, driving times to various hospitals, transfer times and hospital-specific workflow times, in order to generate a transport advice for paramedics. This personalised approach and adaptable framework facilitates implementation across regions with diverse healthcare infrastructures. This study is expected to provide valuable insights into the optimisation of organisation of prehospital stroke care pathways. Moreover, it contributes to a broader understanding of the challenges and opportunities associated with implementing digital health technologies in routine clinical practice. Lastly, the innovative design of the PRESTO-2 study demonstrates that complex implementation studies can be conducted in an efficient and pragmatic manner. In the context of declining availability of research funding and increasing pressure on healthcare accessibility, such innovations may play a pivotal role in sustaining efficient and equitable care delivery.

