### Study population

For the primary objective, we will include all adult patients (≥18 years) with a clinical hospital-confirmed diagnosis of ischaemic stroke who presented to the Emergency Department within 6 h from symptom onset in the 24 months before implementation (January 2022–January 2024) and 24 months after implementation (January 2024–January 2026) of the Stroke Triage App in both the intervention region and the control region. The intervention region consists of approximately 1.8 million inhabitants and 2 ambulance regions (Rotterdam-Rijnmond and Zuid-Holland Zuid), containing 2 intervention centres and 7 referring PSCs. The control region consists of approximately 2.8 million inhabitants and 4 ambulance regions (Zaanstreek-Waterland, Kennemerland, Amsterdam-Amstelland and Noord-Holland-Noord), containing 2 intervention centres and 9 referring PSCs, of which one closed in early 2023. No form of individualised triage was implemented in the control region during the study period, with patients being transported to the nearest IVT-capable stroke centre in accordance with national guidelines. The 2 regions are similar concerning degree of urbanisation and distances between hospitals (Tables 1 and 2).

**Table 1 TB1:** Description of the intervention region.

Hospital	Distance from intervention centre (km)	Estimated driving time (min) ^a^

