**Amsterdam UMC, location AMC**		
**Amsterdam UMC, location VUmc** ^**b**^	10.0	10
**OLVG West**	15.3	14
**Spaarne Gasthuis**	27.9	21
**Flevoziekenhuis**	29.3	24
**Rode Kruis Ziekenhuis**	35.9	26
**Dijklander Ziekenhuis, location Purmerend**	38.3	28
**Dijklander Ziekenhuis, location Hoorn**	56.8	37

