**Noordwest Ziekenhuisgroep, location Alkmaar**		
**Noordwest Ziekenhuisgroep, location Den Helder**	43.1	43

^a^Estimated with ArcGIS Online Software version 10.6.1.

^b^Closed for acute stroke care in the spring of 2023.

For the secondary objective, we will include all consecutive adult patients (≥18 years) with a suspected stroke (based on a positive FAST-test [≥1 point, except for isolated dysarthria]) with onset of symptoms within the last 24 h for whom the Stroke Triage App was utilised in the intervention region during the study period.

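### A control-region stroke centre closed during the before-period, so the argument that distance differences were stable does not hold and difference-in-differences does not remove the change

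*Protocol article*

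**What the plan says.** The Discussion concedes a difference between regions ("Although distances between PSCs and intervention centres differed slightly between regions") and then dismisses it: "these differences were stable over time and are therefore unlikely to bias the estimated intervention effect". The following sentence widens the inference: "we expect the between-region differences before and after implementation to primarily reflect underlying temporal trends". The Data analysis plan says of DID: "This method adjusts for unobserved confounders and (other) time-related differences in acute stroke care".

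The Study population section describes the control region as "containing 2 intervention centres and 9 referring PSCs, of which one closed in early 2023". Table 2 identifies the hospital as "Amsterdam UMC, location VUmc", 10.0 km and 10 min from its intervention centre, with the footnote "Closed for acute stroke care in the spring of 2023". The before-period runs from January 2022 to January 2024. No closure is reported in the intervention region. The article discloses the closure twice but does not connect it to the stability argument or to the DID assumption.

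**The concern.** DID cancels regional differences that are constant over time, and time trends that both regions share. The closure is neither. The control region had this PSC for roughly half to 70% of the before-period and for none of the after-period. To the extent that this shifts control onset-to-groin times, parallel trends fails and the shift is carried, with opposite sign, into the estimated effect of the app.

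The closure reaches the primary outcome. EVT patients are taken from intervention centres only (Data collection), so those first seen at the closed PSC are in the data. Control patients go to the closest hospital able to give thrombolysis. With an intervention centre 10 min away, some would plausibly now go straight there, which is the same pathway change that the app is meant to produce. The onset-to-needle cohort may also change, because patients given IVT count only if they were not transferred.

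At stake is whether the remaining before-after contrast can be read as temporal trend, as the Discussion reads it.

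**Working it through.** The plan gives no figure on this point, so there is none to reproduce. The check has four steps.

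**1. Is the distance difference stable?** These are unweighted means over the PSCs listed in Tables 1 and 2. The text gives 9 control PSCs but Table 2, as readable, lists 8.

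| | Mean km | Mean min | Median min |
|---|---|---|---|
| Intervention (7 PSCs) | 16.7 | 21.7 | 20 |
| Control, with closed PSC (8) | 32.1 | 25.4 | 25 |
| Control, without it (7) | 35.2 | 27.6 | 26 |

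The gap in means moves from 15.3 to 18.5 km, and from 3.7 to 5.9 min, during the before-period. The closed PSC was the nearest to its intervention centre of the 8 listed. The gap is therefore not constant, although its movement in driving time is modest. This tests the wording of the claim; it does not measure the bias.

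**2. Size of the bias.** Let f be the share of the before-period with the PSC open, s its share of control EVT patients, and g the mean change in onset-to-groin time for its rerouted patients.

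DID bias = −(f × s × g)

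- f = 12/24 to 17/24, from the two closure descriptions.
- s = 5% to 20%: assumption.
- g = −30 to −60 min, with every patient now arriving directly: assumption.

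Results:
- Lowest: 12/24 × 0.05 × 30 = 0.75 min.
- Middle: 14/24 × 1/9 × 45 = 2.9 min.
- Highest: 17/24 × 0.20 × 60 = 8.5 min.

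All are toward zero. If rerouted patients instead lose a net 15 min by reaching another PSC first, the bias is away from zero: 12/24 × 0.05 × 15 = 0.4 min up to 17/24 × 0.20 × 15 = 2.1 min.

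If direct arrivals save 30-60 min and the others lose 9-14 min (also assumed), the sign changes at a direct share of loss/(loss + gain). That is 9/(9 + 60) = 13% to 14/(14 + 30) = 32%.

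**3. Against the expected effect.** The planned effect is 31 min. The revision after the interim look can be read as a reduction to 33% (31 × 0.33 = 10.2 min) or by 33% (31 × 0.67 = 20.8 min).

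| Bias | of 31 min | of 20.8 min | of 10.2 min |
|---|---|---|---|
| 0.75 | 2% | 4% | 7% |
| 2.9 | 9% | 14% | 29% |
| 8.5 | 27% | 41% | 83% |

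**4. Precision of a restricted analysis.** Inputs are SD 94.1 min and 800 intervention EVTs per 24 months (2 × 400), both from the article, and 1,200 control EVTs per 24 months (assumption). The ICC is ignored.

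- Full: 94.1 × √(2/800 + 2/1200) = 6.1 min.
- Before-period cut to the last 9 of 24 months (300 and 450 EVTs): 94.1 × √(1/800 + 1/1200 + 1/300 + 1/450) = 8.2 min.
- The data are nested, so the difference between the two estimates has SE √(8.2² − 6.1²) ≈ 5.5 min. Chance alone allows differences up to about 1.96 × 5.5 ≈ 11 min.

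**The case against.** The strongest defence has four parts.

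- **The sentence is about distances, and is hedged.** Individual hospitals did not move, and the article calls bias unlikely, not impossible. A reader might infer that the plan declares all regional differences stable or rules bias out; it does neither. But the set of PSCs changed, and the next sentence extends the argument to before-after differences generally.
- **The regions are similar in driving time.** A reader might take the kilometre contrast (medians 8.9 and 32.6 km) as showing that the regions are not comparable. The driving-time medians are 20 and 25 min, so calling the difference slight is defensible. A constant gap is in any case what DID removes. This part stands: the issue is the change, not the level.
- **The direction is unknown.** A reader might infer that the bias probably hides a benefit. The documents do not say where the closed PSC's patients went, how many EVT patients it referred, or what time was saved. This part also stands.
- **Sensitivity models and trend checks belong in the SAP.** The SAP is in the supplement, was not available here, and may already contain them. So their absence from the article is not the point. The point is a premise that the article states, which an SAP model would not make correct.

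**Conclusion.** The stability argument conflicts with the article's own account of the closure, and the description of what DID adjusts for is too broad. The closure is a control-only change over time that DID does not remove and that can bias the primary estimate.

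Sign and size are not known. The range of about 0.8 to 8.5 min toward zero rests on assumed referral shares and time savings, and on every patient arriving directly. The upper end combines the extremes of all three inputs. Its 83% of the expected effect also needs the smaller reading of the 33% revision, so it should not be quoted as the likely impact. The middle case is about 3 min, which is minor against 31 min and not negligible against about 10 min. This should be corrected, but it does not invalidate the design.

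**What to change.** 1. In the Discussion, replace the stability statement with an acknowledgement that a control PSC closed during the before-period and that this may bias the estimate in either direction.
2. In the Data analysis plan, limit the claim to unobserved confounders that are constant over time and to time trends common to both regions.
3. Give one closure date (the text says early 2023, the footnote spring). Report where that PSC's patients went and how many EVT patients it had referred, if obtainable.
4. Beside the 24-month analysis, report a sensitivity DID whose before-period starts after the closure in both regions, or equivalently a control-by-post-closure term with calendar-time effects, with a pre-trend check. If the SAP already has this, refer to it. If analysis has begun, label it post hoc.
5. Report the difference between the two estimates with its confidence interval. Do not read disagreement automatically as closure bias: chance differences of up to about 11 min exceed the largest bias calculated here.

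The cost is text edits and one secondary model. That model is less precise (SE about 8.2 against 6.1 min, under the assumed control volume and ignoring the ICC). The primary analysis is unchanged.
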